#### Outcomes

##### Primary outcome measure

The primary outcome is the performance time, expressed in minutes. The performance time corresponds to the sum of imaging time and needling time, which both are secondary outcomes. For more details on those times, refer to the secondary outcomes.

##### Secondary outcome measures

Imaging time: will be measured in minutes and corresponds to the time interval between contact of the US probe with the patient skin and the acquisition of a satisfactory image.Needling time: will also be measured in minutes, from the start of the skin wheal to the removal of the block needle from the tissues.Sensory loss at 10, 20 and 30 minutes: will be assessed in the territory of the radial (lateral aspect of the dorsum of the hand), median (volar aspect of the index), ulnar (volar aspect of the fifth finger), musculocutaneous (lateral aspect of the forearm), and medial cutaneous nerve of the forearm (medial aspect of the forearm) distributions using a 3-point score, where 0 = normal sensation, 1 = diminished sensation to pinpricks (hypoesthesia), and 2 = loss of sensation to pinpricks (analgesia). The sum of five scores on a maximum of 10 will be the sensory-loss final score. An independent, blinded, research assistant will complete the sensory assessment at 10, 20 and 30 minutes.Motor block at 10, 20 and 30 minutes: motor function will be tested (0 = normal strength, 1 = weakness, 2 = paralysis) for the radial (wrist extension), median (thumb-fifth finger opposition), ulnar (fifth finger abduction), and musculocutaneous (elbow flexion) nerves. The sum of the four scores on a maximum of 8 will be the motor block final score. An independent, blinded, research assistant will complete the motor assessment at 10, 20 and 30 minutes.Success of plexus block: success is a dichotomic variable answered by yes or no. Success is defined as the completion of surgery without the need for additional LA infiltration, intravenous narcotics, or general anaesthesia. However, light sedation is allowed if deemed necessary by the anaesthesiologist. Light sedation includes midazolam 1 to 4 mg intravenously, fentanyl up to 1mcg/kg. A minimum sensory score of 9/10 will be necessary to proceed to surgery without additional LA infiltration. Patients with an overall sensory score under 9/10 at 30 min will be offered general anaesthesia or supplemental blocks.Total anaesthesia time: is measured in minutes and defined as the sum of performance time and time to achieve a minimum sensory score of 9/10. It is the time for readiness for surgery.Number of block needle passes: is defined as a unit of 1, 2, 3, etc., and is the number of times the block needle will have to be realigned on the skin in order to achieve its final positioning goal under the axillary artery.Needle visualization: procedures will be videotaped and reviewed simultaneously after study completion by 2 independent anaesthesiologists skilled in US-guided regional anaesthesia using a 5-point Likert scale to rate needle visibility (1 = very poor, 2 = poor, 3 = fair, 4 = good, 5 = very good). Needle visibility will be evaluated twice. First, for RCB, assessment will be made when the needle tip is seen 1 cm after crossing the clavicle acoustic shadowing. For the coracoid ICB, the first assessment will be at a needle tip depth of 1 cm. The second needle visibility assessment will be immediately before the local anaesthetic injection, when the visibility is theoretically optimized.Needle angle: using the same videotape that we used for the evaluation of the needle visibility, we will note the angle between the needle and the upper side of the ultrasound image. It will be a continuous outcome ranging from 0 to 90 degrees.Neurostimulation use: neurostimulation is accepted if needed. However, its use other than for a safety sentinel (defined by <0.3 mA) will be recorded for subsequent analysis. It will be a dichotomous outcome.Pain during the procedure: immediately after block completion, patients will be asked to rate their discomfort associated with the procedure using a 10-cm visual analogue scale (0 = no pain, 10 = worst pain imaginable) by an independent and blinded outcome assessor.Early and late complications: the incidence of needle-induced paresthesia, vascular puncture, Horner syndrome, dyspnea, and symptoms of LA toxicity will be noted. All patients will be contacted 48 hours after surgery to ask for any delayed complications, such as dyspnea, paresthesia, weaknesses, pain at the puncture site or haematoma. Patients with complications will be followed up by our research group and a consultation in neurology may be sought.

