#### Interventions

Blocks will be performed by anaesthesiologists experienced in US-guided regional anaesthesia or by PGY-2 to PGY-5 residents under direct supervision by an experienced anaesthesiologist. Operators will have registered a minimum of 25 USG blocks before participating in the study.

Upon arrival in the induction room, standard ASA monitoring will be installed and an 18-gauge or 20-gauge intravenous catheter will be inserted in the contralateral arm. Premedication will be given based on patient preference and the anaesthesiologist’s judgment. Patients will be placed in the supine position with the torso elevated to about 30 degrees and the head facing the opposite side. After a prescan and US parameter optimization, the US probe will then be applied using a sterile technique. A high-frequency linear US probe (6–15 Hz Philips HD11XE Ultrasound; Philips Medical Systems, Bothell, WA, USA, 9–15 Hz Logiq P6; GE Healthcare, Mississauga, ON, Canada, or 15–6 MHz linear probe Sonosite Edge HFL50x; Sonosite Canada inc. Markham, Ontario, Canada) will be used and placed parasagittally just medial to the coracoid process and caudal to the clavicle. Short-axis visualization of the axillary vessels and of the cords will be obtained; the lung and second rib will be identified.

For the retroclavicular approach, the needle insertion point will then be found by palpating the supraclavicular fossa, just medial to the shoulder, at a point sufficiently posterior to the clavicle (generally 1–2 cm depending on morphology and the extent to which the supraclavicular fossa can be depressed) and medial to the trapezius muscle insertion point on the clavicle. This landmark is essential, as the needle will need to clear the clavicle and stay parallel to the US probe to avoid any posterior angling. From this finger position, probe rotation and alignment with the palpating finger will be perfectly achieved while keeping the axillary vessels in the short axis. Once probe rotation achieves finger-probe alignment, the needle will now aim more towards the anterior axillary line than with the coracoid ICB. For optimal imaging and technique the final probe position should rest in the delto-pectoral groove.

For coracoid ICB, the US probe will be applied in the infraclavicular fossa until good visualization of the axillary vessels is obtained and if possible, the brachial plexus cords, then the optimal approach angle and puncture point will be planned.

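### The primary performance time leaves the interval between an undefined satisfactory image and the skin wheal untimed, so arm-specific preparation can escape a comparison whose margin is only 16.8 s

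*Protocol article*

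**What the plan says.** Under Primary outcome measure: "The performance time corresponds to the sum of imaging time and needling time". Under Secondary outcome measures, imaging time "corresponds to the time interval between contact of the US probe with the patient skin and the acquisition of a satisfactory image", and needling time runs "from the start of the skin wheal to the removal of the block needle from the tissues". The first clock therefore stops at one event and the second starts at another, later one.

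The Interventions section describes the preparation. After a prescan, the probe is applied with sterile technique, and for both arms "Short-axis visualization of the axillary vessels and of the cords will be obtained; the lung and second rib will be identified". The arms then diverge:

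- **RCB.** "For the retroclavicular approach, the needle insertion point will then be found by palpating the supraclavicular fossa". From the finger position, "probe rotation and alignment with the palpating finger will be perfectly achieved while keeping the axillary vessels in the short axis". The section then links the best imaging to a final probe position in the delto-pectoral groove.
- **ICB.** The probe is applied until the vessels are well seen, and the approach angle and puncture point are planned after that.

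The Sample size section assumes 45 s of imaging in both arms, performance times of 5 min 36 s (ICB) and 4 min 29 s (RCB), an SD of 2 min 18 s and a margin of 5%. It asks for 49 patients per group, with 55 as the target.

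**The concern.** The primary question is which technique takes longer, and the measured quantity is a sum of two intervals that do not meet. Whatever the operator does between them is not counted. That would be harmless if the untimed work were the same in both arms, but the Interventions section describes different work.

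What is counted depends on when the image is called satisfactory. For RCB, a short-axis view exists before palpation and is maintained during rotation, so the clock could stop before or after alignment. For ICB, good visualization precedes planning, so the planning could go untimed. The article also does not say whether the clock starts at the prescan or at the sterile probe contact.

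Because the margin is under 17 s, a short net difference in untimed work is large relative to what the trial is meant to detect. Untimed RCB seconds push the result towards non-inferiority; untimed ICB seconds push it away.

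**Working it through.** **Inputs (Sample size section).** ICB mean 336 s; RCB mean 269 s as stated; SD 138 s; margin 0.05 × 336 = 16.8 s; one-sided alpha 0.05; power 0.90; 49 per group (target 55). The margin is treated as fixed at its planning value.

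**Reproducing the plan's figure.** Planned difference = 269 − 336 = −67 s, so the distance to the margin is 16.8 + 67 = 83.8 s.

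n = 2 × 138² × (1.645 + 1.282)² / 83.8² ≈ 46.5, so 47 per group. The noncentral t version gives 48. The plan states 49, so its inputs are understood.

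**Effect of an untimed difference.** Let g be the untimed seconds in RCB minus those in ICB. If the true full-time difference equals the margin, the timed difference is 16.8 − g. The chance of declaring non-inferiority is then

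Φ(g/SE − 1.645), with SE = 138 × √(2/n) = 27.88 s at n = 49 and 26.32 s at n = 55.

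The protocol gives no duration for any of these steps, so g is an assumed range. The gap is taken to add no variance. The power column asks what power a test on full elapsed time would have if the planned −67 s holds for the timed sum: Φ((83.8 − g)/27.88 − 1.645).

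| g (s, assumed) | Chance of declaring non-inferiority at the margin, n = 49 | Same, n = 55 | Power on full time, n = 49 | n per group for 0.90 power on full time |
|---|---|---|---|---|
| 0 | 5.0% | 5.0% | 0.91 | 47 |
| 10 | 9.9% | 10.3% | 0.84 | 60 |
| 16.8 | 14.9% | 15.7% | 0.78 | 73 |
| 30 | 28.5% | 30.7% | 0.61 | 113 |

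**The opposite direction.** If ICB planning is the larger untimed part, g is negative and the test becomes conservative for full time. At n = 49, g = −10 gives Φ(−0.359 − 1.645) = 2.3%, and g = −16.8 gives Φ(−0.603 − 1.645) = 1.2%.

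**Alpha.** The Sample size section pairs a 95% confidence interval with one-sided 0.05. If the interval is two-sided, the base rate is 2.5%, and 10, 16.8 and 30 s give 5.5%, 8.7% and 18.8% at n = 49. The pattern is the same.

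**The case against.** A reader might infer that RCB palpation and rotation do fall in the untimed gap and that the measured time therefore favours RCB by more than the margin. The documents do not support that, for four reasons:

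- **The RCB steps may already be timed.** The Interventions section ties optimal RCB imaging to the final probe position, and the view used for needling exists only after alignment. If the clock stops there, palpation and rotation are inside imaging time.
- **ICB also has work that can go untimed.** Its angle and puncture point are planned after good visualization. If RCB is timed through alignment, the bias could run against RCB.
- **No duration is given.** The nearest figure is 45 s for the whole of imaging, so a net excess of 16.8 s would be 16.8/45 = 37% of that. It is possible but not shown.
- **The 10% to 28% figures are not the type I error of the outcome as defined.** For the sum of the two intervals, a valid 5% test stays at 5%. The figures apply to full elapsed time with the true difference exactly at the margin. At the planned −67 s, a 16.8 s shift still leaves RCB about 50 s faster.

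All four points stand and limit the claim.

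It can also be said that stop-clock detail belongs in the standardized data collection document, which is not shown. That may be so for the meaning of a satisfactory image. It does not remove the gap, because the article itself fixes where one interval stops and the other starts. Having a research assistant hold the chronometer helps accuracy, but does not settle which event is timed. Nor does stratification by site remove a timing difference between arms within a site.

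**Conclusion.** The point holds as a defect in the definition of the primary outcome, not as a demonstrated bias in favour of RCB. The untimed interval follows from the stated rules, the work that can fall in it differs by arm, and the margin is 16.8 s. The direction and size of the net difference cannot be derived from the protocol.

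If the net untimed RCB excess were as little as 10 s, the chance of a non-inferiority claim at the margin of full procedure time would about double. At 16.8 s the excess equals the whole margin and that chance about triples. These figures rest on an SD of 138 s, 49 per group, one-sided 0.05, no added variance from the gap, and elapsed time as the quantity of clinical interest. The definition should be tightened while recruitment continues, because untimed seconds cannot be recovered from the two recorded intervals.

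**What to change.** 1. Clarify that in both arms a satisfactory image is the final view before puncture, with the puncture point already chosen. For RCB this means after finger-probe alignment; for ICB, after the angle and puncture point are planned.
2. State which probe contact starts the clock, the prescan or the sterile application, and use the same one in both arms.
3. Record one continuous time from that contact to removal of the block needle, and analyse it against the same margin as a sensitivity analysis. The primary outcome remains imaging plus needling time.

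The cost is small. The Data collection methods section already has a research assistant timing each block with a chronometer, so this needs one instruction, one extra field and a few words in the protocol. If the data collection document already contains such a rule, it only has to be carried into the protocol.

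The drawback is that patients already enrolled (a quarter of the calculated sample at manuscript submission) were timed without the clarification and have no continuous time. Keep them in the primary analysis, and report the result for patients timed after the change as a check. The change should be dated and described as a clarification, made without looking at times by arm, because the trial is open to the operators and the statistician.

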Because a steep-angle needle-ultrasound (US) beam is often required, needle visualization remains a challenge in coracoid ICB, particularly when the needle approaches the neurovascular bundle [8, 9]. Because the needle entry point is different, the recently described retroclavicular (RCB) approach offers an almost perpendicular angle between needle and the US beam [10]. This technique has already been described as efficient, rapid, safe and simple to perform in both a recent study [11] and a recent case series [12]. As such, following the Standard protocol items: recommendation for interventional trials (SPIRIT) clinical trial design recommendations (see Additional file 1) [13], our hypothesis is that when comparing RCB with coracoid ICB for upper limb surgery, both techniques will offer similar outcomes except for needle visibility. We believe that the almost perpendicular needle-US beam angle in RCB will provide superior needle visibility to coracoid ICB.

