#### Needling and injection

Under sterile conditions a skin wheal will be made using a 30-gauge needle, and 2 ml of 2% xylocaïne will be applied either behind (RCB) or below (coracoid ICB) the clavicle. A 100-mm 18-gauge echogenic needle, bevel facing up (Plexolong Nanoline; Pajunk Medizintechnik, Geisingen, Germany) will then be inserted into the skin wheal and advanced strictly in-plane with the US beam.

For RCB the needle will cross an initial blind zone measuring 3–4 cm, which corresponds to the acoustic shadow of the clavicle. For safety purposes, this length should be evaluated by checking the surface distance between the probe and initial insertion point. Once the blind zone is crossed, correct in-plane alignment should enable a precise view of the needle shaft and the tip as it advances towards the neurovascular bundle. If the initial puncture point is correct and the angle of penetration is parallel to the US probe, the shaft should point to the posterior wall of the axillary artery. Most importantly, the needle should clear the posterior wall of the clavicle and must not be angled posteriorly, to avoid any risk of pneumothorax.

For coracoid ICB, the needle will be inserted immediately under the clavicle, through the skin wheal, as established previously. The needle will be angled and advanced while aiming for the posterior wall of the axillary artery.

Hydrolocalization with 5% dextrose and neurostimulation are allowed if deemed necessary. Once the block needle tip is located adjacent to the axillary artery and posterior cord, hydrodissection using a local anaesthesia (LA) bolus will enable safe and efficient spread of LA to initially achieve the double-bubble sign [14].

Mepivacaine 1.5% (20 ml) and ropivacaine 0.5% (20 ml) will be injected in a fractionated way, while slightly adjusting the needle tip to obtain a U-shaped distribution of local anaesthetic around the axillary artery.

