#### Statistical methods

Analysis of the primary outcome: performance time will be analyzed with a non-inferiority test of the averages, with the objective of finding that the experimental RCB approach takes no longer to perform than the coracoid ICB approach.

The secondary outcomes will all be analyzed using superiority analysis. For continuous data or ordinal data with >8 categories, data will be compiled as average and standard deviation. If data are parametric, Student’s *t* test will be used and if not, the Mann-Whitney test will be used. For dichotomous data (block success, use of neurostimulation), the chi square or Fisher exact test will be used if n >5 or is not >5, respectively. Finally, for ordinal data the chi square test will be used if data are parametric, otherwise the Mann-Whitney test will be used.

Subgroup analysis will be conducted to evaluate if higher BMI influences the outcomes of performance time, needle visibility, number of needle passes and needle angle. Patients will be divided in two groups (of those with higher and those with lower BMI than the average BMI of all recruited patients) and analyzed according to their subgroup. If data are missing or if any patients drop out of the study, data will be analyzed using the intention-to-treat principle.

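### The first needle-visibility rating has a different landmark in each arm, and the ordinal-data rule allows an unordered chi-square on a condition that has no meaning for a 5-point score

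*Protocol article*

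**What the plan says.** **Role of the outcome.** The Background of the protocol article states the superiority hypothesis: "We believe that the almost perpendicular needle-US beam angle in RCB will provide superior needle visibility to coracoid ICB". Visibility is listed under Secondary outcome measures, and Statistical methods adds: "The secondary outcomes will all be analyzed using superiority analysis".

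**How it is scored.** Ultrasound recordings are reviewed after study completion by two anaesthesiologists "using a 5-point Likert scale to rate needle visibility", running from very poor (1) to very good (5). "Needle visibility will be evaluated twice".

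- First rating, RCB: "First, for RCB, assessment will be made when the needle tip is seen 1 cm after crossing the clavicle acoustic shadowing".
- First rating, ICB: "For the coracoid ICB, the first assessment will be at a needle tip depth of 1 cm".
- Second rating, both arms: immediately before the local anaesthetic goes in.

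Needling and injection explains the shadow in the RCB landmark: "the needle will cross an initial blind zone measuring" 3–4 cm under the clavicle.

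**How it is tested.** Ordinal data with more than 8 categories are handled like continuous data. For the rest, Statistical methods says: "for ordinal data the chi square test will be used if data are parametric, otherwise the Mann-Whitney test will be used".

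The article does not say which of the two ratings decides the visibility hypothesis.

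**The concern.** An outcome that compares two techniques should be measured at a point defined independently of the outcome itself, and in the same way in both arms. Taken at its word, the first RCB rating waits until the tip is visible, and visibility is what is being rated. The ICB wording contains no such condition. If RCB procedures with an unseen tip at that point are rated later or not at all, the lower end of the RCB distribution is thinned and the comparison can lean towards the hypothesised winner. The two ratings also sample different stretches of the needle path.

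The test rule is a separate weakness. Five ordered categories cannot meaningfully be called parametric. Even if they could, a test that ignores their order would not follow. As written, the rule leaves a choice of test to judgement, and the Blinding section says that the statistician is not blinded.

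At stake is whether the superiority statement on visibility can be believed and whether it is tested efficiently. The non-inferiority conclusion on performance time is not at stake.

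**Working it through.** **1. The plan's own figure.** No effect size, power or sample size is given for visibility. The only relevant stated number is 49 per group, from the primary outcome (Sample size section). With ICB time 5.60 min, RCB time 4.483 min, SD 2.30 min, margin 5% × 5.60 = 0.28 min, one-sided 0.05 and power 0.90:

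n = 2 × (1.645 + 1.282)² × 2.30² / (0.28 + 1.117)² ≈ 46.4, so 47 per group.

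This is within two patients of 49. The figure is not disputed here and is used below only as the group size.

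**2. The landmarks side by side.**

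| | RCB | ICB |
|---|---|---|
| First rating: position | 1 cm past the clavicle shadow, so about 3 + 1 = 4 to 4 + 1 = 5 cm along the path | tip depth of 1 cm |
| First rating: condition on visibility | tip is seen (literal reading) | none stated |
| Second rating | just before injection | just before injection |

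Only the first row pair differs between arms.

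**3. How large could the conditioning effect be?** The article does not say how often the tip is unseen, so this is a range under assumptions. Assume equal true visibility in both arms, that the lowest score cannot occur in RCB, and that ICB carries no condition. If p is the proportion scored 1 and μ the mean score, removing category 1 raises the RCB mean by p(μ − 1)/(1 − p). Scores 2, 3 and 4 are assumed at 20%, 30% and 30%, with the remainder in 5. Simulated false-positive rates use 49 per group, two-sided 0.05 and 3,000 runs.

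| p | μ | Spurious rise in mean | Mann-Whitney | Chi-square |
|---|---|---|---|---|
| 5% | 3.30 | 0.05 × 2.30 / 0.95 = 0.12 | 7% | 10% |
| 10% | 3.10 | 0.10 × 2.10 / 0.90 = 0.23 | 14% | 30% |
| 15% | 2.90 | 0.15 × 1.90 / 0.85 = 0.34 | 26% | 64% |
| 20% | 2.70 | 0.20 × 1.70 / 0.80 = 0.43 | 43% | 92% |

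These rates show what the literal reading could do. They do not estimate what this trial would do.

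**4. What does the chi-square branch cost?** Scores were generated from a normal latent variable cut at −1.5, −0.7, 0.2 and 1.0, with the RCB arm shifted. All of this is assumed. Power at 49 per group, two-sided 0.05, 3,000 runs:

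| Shift (SD) | Mann-Whitney | Chi-square |
|---|---|---|
| 0 | 4.9% | 4.3% |
| 0.4 | 45% | 26% |
| 0.5 | 62% | 40% |
| 0.6 | 79% | 56% |
| 0.7 | 89% | 71% |

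The loss is 18 to 23 percentage points. At 55 per group it is similar (0.5 SD: 68% against 45%; 0.6 SD: 82% against 61%). A proportional-odds model with assumed ICB scores of 8/17/30/30/15% gave 84% against 64% at an odds ratio of about 3, and 76% against 54% at about 2.7 (4,000 runs each). The zero-shift row shows that the chi-square branch loses power but does not by itself inflate type I error.

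**The case against.** A reader might infer that the visibility comparison is biased towards RCB by construction. The documents do not support that, for four reasons.

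- Only the first of two ratings is affected. A comparison on a common landmark is already planned.
- The RCB wording can be read as position only, meaning a tip 1 cm beyond the shadow. The conditioning then shrinks, although the landmarks still differ. The ICB wording is silent on an unseen tip. A rater working from the recording may need to see the tip to place it at 1 cm, so ICB could carry an implicit condition of its own.
- The position difference may work the other way. The Background says that ICB visualization is hardest as the needle nears the neurovascular bundle, and a rating at 1 cm depth comes before that stretch. This could favour ICB.
- A barely discernible tip can still be scored 1, so the assumption in step 3 that this score cannot occur in RCB is an extreme one.

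A reader might also infer that chi-square will be used. Mann-Whitney is already the other branch and is the natural reading for a 5-point score. If the two raters' scores were averaged, nine values would be possible (1 to 5 in halves), and the rule for more than 8 categories would apply instead. Nor is it right that a chi-square hides which arm did better. The test has no direction, but the table shows it.

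The two independent raters are said to review simultaneously. That is ambiguous and does not show joint scoring. The abstract speaks of two separate persons ranking visibility.

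What stands: the first landmark differs by arm on any reading and admits a literal reading that conditions on the outcome. The article does not say which rating carries the claim. The test rule turns on a condition that cannot be applied.

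**Conclusion.** The point holds for the first rating and for the wording of the ordinal-data rule, and is worth correcting before scoring. It concerns a secondary outcome, though one that carries the superiority hypothesis.

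The "First, for RCB, assessment will be made when the needle tip is seen 1 cm after crossing the clavicle acoustic shadowing" condition can favour RCB. Because the positions also differ, the net direction and size of bias cannot be determined from the document. The false-positive range of 7–43% with Mann-Whitney applies only if 5–20% of needles would score 1, that score is impossible in RCB, and ICB is unconditioned.

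If the chi-square branch were taken, power would be about 20 percentage points lower than with Mann-Whitney at 49 per group. That figure rests on assumed score distributions and a two-sided 5% level, since the article gives no visibility data.

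**What to change.** 1. State that the superiority claim on visibility rests on the pre-injection rating, which is defined identically in both arms.
2. Define the first rating in both arms by needle position, whether or not the tip is seen. Score an unseen tip as 1 and treat this rating as supportive. The rater instructions should say how the frame is chosen when the tip cannot be located on the recording.
3. Delete the chi-square branch for the visibility score and name Mann-Whitney, or a proportional-odds model.

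Optional: stratify the test by site (van Elteren), average the two raters, and state that they score separately.

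The cost is reworded rater instructions and one changed sentence in the statistical methods. Videos are rated only after study completion, so both can be settled before any score exists and nothing has to be collected again. The downside is that the first rating no longer carries the claim.
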